## Abstract

**Background:**

Dementia is increasing in prevalence as the population ages. An earlier rather than later diagnosis allows persons with dementia and their families to plan ahead and access appropriate management. However, most diagnoses are made by general practitioners (GPs) later in the course of the disease and are associated with management that is poorly adherent to recommended guidelines. This trial examines the effectiveness of a peer led dementia educational intervention for GPs.

**Methods:**

The study is a cluster randomised trial, conducted across three states and five sites. All GPs will complete an audit of their consenting patients aged 75 years or more at three time points - baseline, 12 and 24 months. GPs allocated to the intervention group will receive two educational sessions from a peer GP or nurse, and will administer the GPCOG to consenting patients at baseline and 12 months. The first education session will provide information about dementia and the second will provide individualised feedback on audit results. GPs in the waitlist group will receive the RACGP Guidelines by post following the 12 month audit

Outcomes: Primary outcomes are carer and consumer quality of life and depression. Secondary outcomes include: rates of GP identification of dementia compared to a more detailed gold standard assessment conducted in the patient's home; GP identification of differential diagnoses including reversible causes of cognitive impairment; and GP referral to specialists, Alzheimers' Australia and support services. A "case finding" and a "screening" group will be compared and the psychometrics of the GPCOG will be examined.

Sample size: Approximately 2,000 subjects aged 75 years and over will be recruited through approximately 160 GPs, to yield approximately 200 subjects with dementia (reducing to 168 by 24 months).

**Discussion:**

The trial outlined in this paper has been peer reviewed and supported by the Australian National Health and Medical Research Council. At the time of submission of this paper 2,034 subjects have been recruited and the intervention delivered to 114 GPs.

**Trial registration:**

Australia and New Zealand Clinical Trials Register (ANZCTR): ACTRN12607000117415.

## Background

### Importance of dementia as an issue

Dementia is an increasingly common condition largely due to increasing longevity of the population in Australia, and other countries. Approximately 1 in 5 Australians over the age of 80 have some form of dementia [1]. By 2050 the number of adults 65 to 84 years with dementia is expected to double and the number of people 85 years or older will more than quadruple [2]. Consequently, the number of people living with dementia is anticipated to rise rapidly. It is forecast that almost 1 million Australians will suffer from dementia by 2050, up from 250,000 in 2009 [1].

Dementia is associated with substantial economic, social and emotional burden. The disease is costly in terms of the need for support services whether sufferers live at home or in residential aged care, as well as in terms of lost productivity for carers and people living with dementia [3]. The *2010 Intergenerational Report *estimates that Australian Government spending on aged care will increase from 0.8 per cent of GDP in 2010 to 1.8 per cent by 2050 [2]. In addition to the effect of dementia on the public and private purse, the emotional suffering both of those with the disease and of their families should not be overlooked.

### The role of the GP in identifying and managing dementia

General practitioners (GPs) appear well positioned as the first point of contact for older persons seeking health care, including those living with dementia. In the decade between the 2000 and 2010, the number of patients aged under 45 years seen annually by GPs increased by 190,000, whereas the number of patients aged 45 years and over increased by 16 million [4]. Twenty-eight percent of the 98,800 encounters recorded by the annual *Bettering the Evaluation And Care of Health *(BEACH) survey of GP consultations from April 2009 to March 2010 were with patients aged 65 and over [5].

General practitioners often make the diagnosis of dementia some considerable time into the course of the disease [6,7]. However, earlier recognition of symptoms can allow reversible causes of cognitive decline to be addressed and identification and management of co-morbidities (e.g. depression). An early diagnosis also allows patients time to plan for the future (e.g. prepare wills, appoint enduring powers of attorney and guardians, prepare advance directives) while they are still competent to do so. Referral can be made to appropriate support services and diagnostic centres for further assessment and/or diagnostic confirmation. Anti-dementia medication that may slow the course of cognitive decline may be trialled. Education for patients and families, along with peer services and support groups, may help them understand and cope with the challenging symptoms of dementia. The support role is particularly stressful [8] and such assistance might reduce support person morbidity such as depression, and prepare them for maintaining people with dementia at home longer [9].

General practitioners often fail to identify dementia early in the course of the disease and also adhere poorly to published dementia guidelines [10,11]. They often fail to exclude other possible causes of cognitive impairment, including physical illnesses, medications and depression [10]; are slow to communicate the diagnosis to patients and carers [12,13]; and fail to refer people on to services, support groups, memory clinics or other specialist resources [10].

### Addressing barriers to diagnosis and guideline adherence

Both qualitative and quantitative research suggests a range of reasons for late diagnosis and otherwise poor adherence to guidelines by GPs [14]. The barriers specifically addressed in this study are the limited time for consultation [15], lack of relevant knowledge [16] and attitudinal factors [13,17]. The GPCOG is a brief screening test developed and refined by team members to address the time constraints in general practice consultations [18]. The Australian *Care of Patients with Dementia in General Practice Guidelines *[19] were developed and trialled in consultation with GPs to assist them in the management of dementia. These guidelines form the basis for the education used in this study. The reluctance amongst GPs to diagnose a disease which lacks a known cure and causes immense suffering to those who have it and their families [13,17] is also addressed in the educational intervention.

### Screening vs case finding as a means of identifying dementia

In general, medical advisory groups and policy makers recommend case finding (further testing only for those who are perceived by the GP as having symptoms suggesting possible dementia) rather than broadly screening persons over a certain age for dementia [20,21]. It is thought that screening in this low prevalence population would result in false positives, causing distress to the patient and their support person, as well as being a burden to the healthcare system. Other guidelines have withheld judgment as they claim insufficient evidence for or against screening [21,22]. This study will compare screening and case finding approaches to identifying dementia.

### Rationale for the educational intervention

This trial addresses the problems outlined above with an interactive educational intervention for GPs, which is described in detail below. The education includes visits by a peer health professional educator and an audit with feedback. The small positive effects of educational meetings [23] can be improved if they are interactive [24]; outreach visits have shown promise in modifying the behaviour of professionals [25]; and audit and feedback has been shown to result in modest improvements in outcomes [23,26].

### Aims of the study

1. Compared to a GP group which does not receive peer delivered education, to examine whether training in and use of a dementia screening instrument and relevant information (see *The Intervention *section below) improves:

i. GP identification (diagnosis) of dementia

ii. Distinction by GPs between dementia and other diseases, including depression (hereafter termed "differential diagnosis")

iii. GP elimination of reversible causes of cognitive impairment

iv. Active management of dementia by GPs as evidenced by increased referral to appropriate services, to Alzheimer's Australia and/or to medical specialists for memory problems where indicated.

Outcomes for consumers and their support people in terms of quality of life (primary outcome), depression (primary outcome), satisfaction with care, and access to Alzheimer's Australia, appropriate services or specialists when indicated.

2. To determine whether a screening or a case finding approach to dementia results in:

i. better outcomes for people with dementia and their carers

ii. a more acceptable process for consumers, support people and GPs

3. o test the psychometric properties of the GPCOG including inter-rater reliability, test-retest reliability and comparison with the MMSE..

## Methods/Design

### Study Design

The trial is a cluster randomised study (summarised in Figure 1). Practices allocated to the Intervention group will receive two dementia related educational detailing visits from a peer GP or a nurse, and complete three audits with feedback. Waitlist practices will complete three audits without feedback and will be mailed RACGP Dementia Guidelines (including the GPCOG) at 12 months.

**Figure 1 F1:**
[figure not shown]
**Summary of recruitment, randomization and study design**.

### Setting

Recruitment will occur across 5 sites: Newcastle (NSW), Sydney (NSW), Melbourne (Victoria), Adelaide (South Australia) and Bendigo (Victoria). Sydney, Melbourne and Adelaide are state capital cities of more than a million people each, Newcastle is a regional centre of around 300,000 people and Bendigo is a smaller centre of just under 100,000 people with some smaller surrounding towns.

### Recruitment of participants

#### GPs

With the exception of Bendigo (which will also include nearby towns as noted above) each site will generate a list of possible GP practices within 30 km of the site headquarters based on lists provided by the local Division of General Practice. Practices will be allocated a random approach order, and will be contacted via phone initially. GPs who express an interest in participation will be visited in order for the study to be explained. Basic demographics will be collected at this visit, from those GPs that agree to participate. It is not expected that all the GPs in a practice will participate. When one or more GPs in a practice consent, the practice as a whole will be allocated to either the intervention or waitlist group. Randomisation will occur at a practice level in order to avoid contamination from patients visiting several GPs who had been randomised to different arms within a single practice.

Randomisation will follow procedures outlined in the CONSORT statement [27]. Practices will be allocated in a ratio of 2:1 to the Intervention or Waitlist group, using an allocation schedule provided independent of the study team, by the Centre for Epidemiology and Biostatistics at the University of Newcastle. The randomisation code has been developed using a computer random number generator to select random permuted blocks. Block lengths of 3 or 6 will be varied randomly. Practices will be stratified by site, and by size of practice as either standard or large (large = more than 7 GPs working in the practice). The intervention group will be kept at twice the size of the waitlist group in order to have sufficient power to compare the effects administering the GPCOG on case finding versus screening patients (see explanation below).

Inclusion criteria for GPs/practices

• Located within 30 kilometres of recruitment centre (with the exception of Bendigo, a rural town)

• Consent to participate in study

• Have patients on a computerised database

• Have patients aged 75 years and over and living in the community

• Consent to being randomised to either intervention waitlist group.

Exclusion criteria for GPs/practices

• Involved in project development

• Does not meet inclusion criteria

### Patients and support persons

Patients will be recruited by a mail out from each consenting GP to all eligible patients on their database. Patient participants will return their consent in reply paid envelopes to the study centre. Patients will be interviewed by study personnel blind to the group allocation of the patient and their GP. For patients scoring in the dementia range on the CAMCOG instrument (described below), the interviewer will request that they nominate a support person, if available, to take part in the study. Nominated support people will be given a consent form and information sheet for recruitment into the study.

Inclusion criteria for patients:

• Aged 75 years or over

• Listed on participating GPs' databases

• Visited recruited GPs within the last 24 months

• Consent to a home visit or surgery visit by project staff

• Speak and understand English

Inclusion criteria for support persons:

• Identified as a carer or support person by a patient scoring in dementia range on CAMCOG instrument

• Prior consent from the person with dementia for his/her carer to participate in the study

• Speak and understand English

• Consent to a home visit or surgery visit by the project staff.

Exclusion criteria for patients:

• Parkinson's disease, multiple sclerosis, motor neuron disease or central nervous system inflammation

• Psychotic symptoms prior to recruitment

• Developmental disability

• Insufficient English to complete a psychometric assessment (judged by interviewer)

• Progressive malignancy

• Substance abuse

• Deemed too sick to complete study by the GP

• Lives in a residential aged care facility at entry to the study

• Does not meet inclusion criteria

• Valid and informed consent cannot be obtained from the person involved and they do not have a person responsible for them.

Exclusion criteria for support persons:

• Insufficient English to complete testing (judged by the interviewer)

• Non-consenting patient-participant

• Does not consent to a home visit or surgery visit by the project staff.

• Too unwell to participate

• De not meet inclusion criteria.

### Case finding and screening

"Case finding" patients will be identified during the patient interview using the following 4 questions:

1. Do you have any complaints about your memory?

2. Have you mentioned these to you GP?

3. If not, have you been intending to tell your GP?

4. Have you sought treatment or taken any remedies such as herbal medications or vitamins specifically for you memory? Please give details.

If questions 2, 3 or 4 are answered in the affirmative, the patient will be considered as a "case finding" patient. Patients identified as having possible or probable dementia on the GP baseline audit will also be considered as a "case finding" patient. All other patients will be identified as "screening" patients - that is, patients who would not receive a cognitive function test unless the GP decided to screen all patients aged over a certain age.

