#### GP audit

GPs will be sent a list of their participating patients by fax or email. They will be asked to confirm each patient's eligibility for the study and to provide their clinical judgement in relation to each patient's dementia status using one of four options: No Dementia, Possible Dementia, Probable Dementia or Definite Dementia. GPs will be asked to complete a supplementary audit for any patients with possible, probable or definite dementia to gather data on differential diagnosis (e.g depression), memory-related tests and investigations performed (i.e. paper and pencil test; pathology; radiology) and referrals to services and specialists. GPs will return their completed audit forms to local project officer via mail, fax or email. GPs will complete audits at baseline, 12 and 24 months.

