#### Does case finding or screening produce better results?

Within the Intervention group, the patient outcomes for the group with memory complaints or identified by the GP as having possible or probable dementia (case finding group) will be compared with outcomes for the group without memory complaints or identified memory problems (screening group). Acceptability of the process and satisfaction with care will be particularly examined, both from a quantitative and a qualitative point of view. The performance of the GPCOG in the case finding and screening groups will be compared. In particular positive predictive value, negative predictive value and misclassification rates will be compared. GP audits will be examined to determine how many patients in each group would have a missed diagnosis of dementia if the GPCOG had not been administered.

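### The case-finding rule omits the GP rating of definite dementia, so some patients the GP already regards as having dementia are classed as screening patients

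*Protocol article*

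**What the plan says.** **GP audit.** GPs rate each participating patient as one of "No Dementia, Possible Dementia, Probable Dementia or Definite Dementia". Where this section means every level of dementia it lists all three: the supplementary audit is for "any patients with possible, probable or definite dementia".

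**Case finding and screening.** There are two routes into the case-finding group.
- Interview: "If questions 2, 3 or 4 are answered in the affirmative, the patient will be considered as a" case-finding patient. Question 1, "Do you have any complaints about your memory", is asked but is not part of the rule.
- Audit: "Patients identified as having possible or probable dementia on the GP baseline audit will also be considered as a" case-finding patient.

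The remainder is a default: "All other patients will be identified as" screening patients. The section explains these as people who would have no cognitive test unless the GP tested everyone above some age.

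**Does case finding or screening produce better results?** The case-finding group is here "the group with memory complaints or identified by the GP as having possible or probable dementia". The screening group is described as having neither memory complaints nor an identified memory problem. The comparison is made within the intervention arm.

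**Outcome measures.** For the second aim, the two groups are compared on the primary outcomes and on secondary outcomes 1 and 2, with a reference back to the definition given earlier.

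**The concern.** The audit route uses the two middle ratings and leaves out the highest one, and the default then sends whoever is left to screening. A patient whose dementia the GP regards as certain can thus enter the group meant to represent cases that only universal testing would reach. It needs a no to questions 2, 3 and 4, which is plausible when a person with dementia lacks insight into the problem.

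Such patients can be enrolled. The patient exclusion criteria do not mention known dementia, and inability to consent excludes only when there is also no person responsible.

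The split carries the whole second aim. It is the stated reason for 2:1 allocation (Recruitment of participants, GPs), and Sample size assumes it divides participants about equally. It also defines the groups in which the GPCOG's predictive values and misclassification rates are compared.

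**Working it through.** No figure in the plan needs reproducing. The check is to apply the two written definitions to every possible patient.

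**Inputs.** Questions 1 to 4 (yes/no) and the four audit ratings. Questions 2 and 3 can be yes only if question 1 is yes, and question 3 only if question 2 is no. That leaves 2 answer patterns with question 1 no and 6 with question 1 yes: 8 patterns × 4 ratings = 32 profiles.

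**Rules.**
- Definition section: case finding if question 2, 3 or 4 is yes, or the rating is possible or probable; otherwise screening.
- Analysis section, read literally: case finding if question 1 is yes, or the rating is possible or probable; screening if question 1 is no and the GP has identified no problem; otherwise neither.

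**Result.** The two sections disagree on 5 of the 32 profiles:

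| Rating | Q1 | Q2 and Q3 | Q4 | Definition section | Analysis section |
|---|---|---|---|---|---|
| Definite | no | no | no | screening | neither |
| Definite | yes | no | no | screening | case finding |
| Definite | no | no | yes | case finding | neither |
| No dementia | yes | no | no | screening | case finding |
| No dementia | no | no | yes | case finding | screening |

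Of the 8 profiles rated definite, the definition section sends 2 to screening (the first two rows). The analysis section puts neither of those in screening. Profiles are counted, not patients; the documents give no frequencies.

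**After adding definite to both sections:** the three definite rows become case finding under both, and two conflicts remain (the last two rows). **After also using the question 2, 3 or 4 rule in both:** none remain.

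**Effect on predictive value.** PPV = Se·p / [Se·p + (1 − Sp)(1 − p)], where p is the prevalence of dementia in the group. For fixed sensitivity and specificity, PPV rises with p and NPV falls. Known cases placed in screening raise p there, provided the CAMCOG standard largely agrees with the GP's definite rating.

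**Scale.** Sample size plans 112 intervention patients with dementia, about half of them screening: 112 × 0.5 = 56. Each misplaced patient with dementia is 1/56 = 1.8% of that group.

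**Illustration of dilution only.** Borrow the plan's 7% difference as 7 points, its SD of 18.5 and its correlation of 0.7. The SD of change is 18.5 × √(2 × (1 − 0.7)) = 14.33. Take 56 v 56, two-sided 5%, no clustering. If a share m of the screening group resembles the case-finding group, the difference shrinks to 7 × (1 − m):

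| m | Difference | Power |
|---|---|---|
| 0 | 7.00 | 0.73 |
| 5% | 6.65 | 0.69 |
| 10% | 6.30 | 0.64 |
| 20% | 5.60 | 0.54 |

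The true m is not in the documents.

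**The case against.** **It is only a drafting slip.** Probably so. The description of screening patients in the definition section and the no-identified-problem wording in the analysis section both show that known dementia was not meant to count as screening. But the two-rating wording appears in both sections, and the default makes the gap operative: an analyst who codes the rule as written reproduces it.

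**The complaint conflict is already settled.** Largely true. Outcome measures refers back to the earlier definition, which is the question 2, 3 or 4 rule. A reader might infer that the analyst is free to choose between two definitions; that goes too far. What stands is a wording conflict in the analysis section. This defence does not help with the definite rating, because that gap lies in the definition itself.

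**Known cases belong to neither strategy.** The Background describes case finding as further testing of patients whom the GP perceives as having possible symptoms. A patient already rated definite fits that poorly, and moving such patients to case finding raises prevalence and PPV there by the same mechanism. This stands, and is why they should also be shown separately.

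**The harm can be overstated.** A reader might infer that screening's yield is inflated. The yield analysis described counts diagnoses that would have been missed without the GPCOG, judged from the GP audits; a patient the audit rates definite is not a missed diagnosis and adds nothing to that count. A reader might also apply the problem to all 2,000 participants, but the outcome comparison is within the intervention arm. Only the acceptability comparison is not limited in that way.

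**Conclusion.** The point holds. As written, the rule classes a patient rated definite as screening whenever questions 2, 3 and 4 are all answered no, against the protocol's own description of that group. This contaminates the second aim's outcome comparison and raises the GPCOG's positive predictive value in the screening group. The PPV statement assumes fixed sensitivity and specificity and reasonable agreement between the GP's definite rating and the CAMCOG standard.

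The size cannot be stated. One might suppose that 10% to 20% of the 112 are rated definite and that a third to two thirds of those answer no, giving 112 × 0.10 × 0.33 = 3.7 to 112 × 0.20 × 0.67 = 15.0 patients, or 7% to 27% of 56. Neither input is in the protocol, so the conclusion does not rest on that range.

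Nothing here touches the randomised intervention versus waitlist comparison. The memory-complaint mismatch is real but secondary.

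**What to change.** 1. In Case finding and screening, and in the analysis section on case finding versus screening, let the audit criterion name all three dementia ratings at baseline: possible, probable and definite. No patient rated definite is then counted as screening.
2. Report the by-group GPCOG results with patients rated definite shown separately, so that known cases do not drive the case-finding group's predictive value unseen.
3. Reword the analysis section to use the definition's rule (yes to question 2, 3 or 4) in place of its general reference to memory complaints. This settles both the patients with yes to question 1 only and those with no to question 1 but yes to question 4.

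The cost is wording changes in two sections, one recode before analysis and one additional breakdown in the GPCOG tables. The audit ratings and all four answers are already collected, and no sample size figure changes.
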